### Sample size and power

With the proposed design, we have > 80% power to detect four scenarios of treatment-related changes in mean Z-score of 0.93–1.66 accounting for multiple testing with a family-wise Type I error rate < 5%. Notably, we have 80% power to detect a difference between exercise and exercise + NR (Scenario 1) of 0.73 Z-score. We have demonstrated that increases in muscle group specific strength of up to 100% (absolute amount) over 24 weeks are plausible, depending on the degree of initial deficits and muscle group tested [45]. In a 12-week pilot study, a mean increase of quadriceps strength of 14% was observed [46]. In a previous meta-analysis in adults, effect sizes of 0.53–0.79 were reported with supervised aerobic exercise [47, 48]. We anticipate that increases in the present study may be even larger for several reasons. First, these relatively young participants will have substantial muscle deficits, thus there is a clear opportunity to demonstrate benefit. Our preliminary data indicate muscle deficits in HCT survivors, with low Z-scores for muscle area (mean -0.9, SD 1.4). Also, we have chosen to intervene at the soonest potential opportunity post-HCT, thus we expect muscle deficits will be less established and participants will be more responsive to the interventions. Our team has considerable experience in supervising, individualizing, and adjusting the exercise regimen to achieve maximum benefit. Also, we will randomize 80 participants to achieve 64 (*n* = 16 in each of 4 arms) with complete data (i.e., conservatively allowing 20% attrition) {14}.

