### Participants and randomization

Potentially eligible participants will be identified and recruited both at CHOP and COH through existing databases and physician referrals. Study staff will pre-screen potential participants by reviewing the medical charts and exclude those who do not meet inclusion/exclusion criteria {15}. Individuals who meet the eligibility criteria (Table 2) will be invited to enroll. All participants will be enrolled when they provide written consent to the principal investigator(s) either virtually or in-person and all the initial eligibility requirements are met {26a}. Once eligibility is confirmed via in-person screening procedures, participants will be randomized into one of four arms, with randomization stratified by age (≥ 18y or < 18y) and site (CHOP or COH) by a designated study member using REDCAP randomization scheme (Fig. 2) {16b} {16c}. Balance between arms will be maintained through randomly permuted blocks of size four or eight {16a}. The research team, outcomes assessors, care providers, and participants will be blinded with respect to whether participants are receiving NR vs. placebo. NR and placebo are dispensed in identical capsules to avoid un-blinding. The outcomes assessor (but not the study team, care providers, or participants) will be blinded with respect to whether individuals are receiving the in-home exercise intervention vs. no exercise intervention {17a}. The Investigator will be unblinded only if an AE occurs that is determined to be serious, and treatment for the adverse event (AE) depends on knowing the group assignment. Participants/families will be unblinded at the completion of the entire study {17b}. The current study has been approved by the Institutional Review Board of Children’s Hospital of Philadelphia (approval number: IRB #17,320) and has been pre-registered at www.clinicaltrials.gov (NCT05194397). The Standard Protocol Items: Recommendations for Interventional Trials (SPIRIT) guideline was used to generate the report [27].

**Table 2 Tab2:** Inclusion and Exclusion Criteria {10}

Inclusion Criteria	Exclusion Criteria

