1. Males and females, ages 15–30 years at enrollment 2. Able to understand and speak English (in order to appropriately follow the intervention) 3. Diagnosis of acute leukemia (myeloid, lymphoid) requiring allogeneic HCT 4. 6–24 months from allogeneic HCT 5. Females must have a negative urine/serum pregnancy test and must use an acceptable method of contraception, including abstinence, a barrier method (diaphragm or condom), Depo-Provera, or an oral contraceptive, for the duration of the study 6. Parental/guardian permission (informed consent) and if appropriate, child assent	1. Known sensitivity to NR 2. Concurrent use of any medications, including statins, likely to increase risk of NR toxicity {11d} 3. Active malignancy, investigational agent(s) within 4 wks, or systemic glucocorticoids within 12 wks 4. Currently meeting public health exercise guidelines 5. Use of NAD^+^ precursors (supra-physiologic) within 4 weeks 6. Hemoglobin < 10 g/dL 7. Platelets < 50 K 8. Diabetes Mellitus requiring insulin or insulin secretagogue 9. HbA1C ≥ 8% 10. Kidney disease (eGFR < 60 ml/min/1.73 m2) 11. Liver disease (ALT/AST > 3 × ULN) 12. Limitations in physical function preventing exercise testing/training 13. Contraindications to MRI 14. Unstable angina or history of acute myocardial infarction (< 5 days of planned study procedures) 15. Recurrent syncope 16. Symptomatic severe aortic stenosis 17. Uncontrolled arrhythmia causing symptoms 18. Pulmonary embolus < 3 months of study procedures 19. Thrombosis of lower extremities 20. Symptomatic moderate or severe persistent asthma based on FEV from pre-HCT pulmonary function testing 21. Room air desaturation at rest ≤ 85% 22. Females: Pregnant or planning pregnancy 23. Non-cardiopulmonary disorders that may affect exercise performance or be aggravated by exercise (e.g., infection, renal failure, thyrotoxicosis, > moderate GVHD resulting in physical or functional impairment) 24. Parents/guardians or subjects who, in the opinion of the Investigator, may be non-compliant with study schedules or procedures

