### Statistical considerations

Linear mixed-effects modeling will be used to evaluate effect of interventions over time on the primary and key secondary outcomes. The models incorporate subject-specific random effects to account for within-subject correlation due to repeated measures. Group averages, as well as subject-specific intercepts and slopes, will be estimated to capture potential variations in the baseline values and slopes among individuals. Linear mixed-effects models accommodate missing data due to dropout, such that all randomized participants can be included. We will compare participants who complete the study with those who do not and identify potential factors that are associated with dropout {20c}. In the mixed-effects models, we will adjust for time-invariant covariates (age at randomization, sex) and time-varying covariates (muscle strength, lean mass, muscle OXPHOS capacity, VO2max). By including these indices of “muscle quality” as covariates in the models, we will be able to assess whether intervention effects are explained by these effects. To assess other potential factors influencing outcomes, we will also analyze the incremental effect of adding each of the other measured covariates (final dose of NR achieved, final training intensity achieved) to the models.

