The primary outcome for our study is the change in muscle strength (quadriceps extension, Z-score) from baseline to 16 weeks. We expect exercise and NR to each produce an increase (relative to control/placebo) with respect to the primary outcome of muscle strength from baseline to week 16. We posit that the effects of exercise and NR in combination will be additive and possibly even synergistic. Despite our strategies to track and optimize adherence, it is possible that the change in Z-score will vary across participants in response to one or both interventions. We will fit a linear model with the outcome of change in Z-score of muscle strength and covariates of treatment arm and baseline Z-score. Using a modification of previous strategies for the analysis of factorial designs, the family-wise Type I error rate is maintained at < 5% by using a two-stage approach: a Holm-Bonferroni correction is applied in Stage 1, and a single contrast is pre-specified in Stage 2 [43]. In Stage 1, we will test if the mean Z-score in each of the 3 active treatment arms differs from control (no-exercise + placebo). In Stage 2, if the exercise + NR arm differs from the control arm, we will then compare exercise + NR to exercise alone, to determine whether NR increases mean Z-score beyond the effect of exercise alone; 95% confidence intervals will be determined for each effect of interest.

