In secondary analyses, we will seek to identify disease covariates and physiological factors (e.g., low muscle OXPHOS capacity at baseline) that are associated with treatment response [44]. With respect to additional outcomes, we anticipate that strength in other muscle groups, lower extremity muscle mass (measured via DXA), and muscle OXPHOS capacity (measured via CrCEST), will all increase in response to both interventions, and in statistical models will demonstrate independent contributions to the observed increases in muscle strength (primary outcome) and other key outcomes. In addition, blood metabolomics will show correlates of increased OXPHOS capacity (e.g., decreased acylcarnitine related to improved fatty acid oxidation capacity, organic acid profiles consistent with increased TCA cycle anaplerosis, and increased CoA species). Even if we do not detect changes in response to either of these interventions, our mechanistic assessments will produce an integrated understanding of the factors associated with low muscle mass, strength and OXPHOS in HCT survivors. The safety data will be an ancillary benefit to guide clinicians caring for HCT survivors who may be considering taking this supplement. The primary analysis will be repeated with each secondary outcome. Additional models will explore whether change from baseline can be explained by either baseline demographic or clinical covariates (age at randomization, sex, key clinical characteristics such as anthracycline and/or steroid exposure, age at HCT, TBI, GvHD grades II-IV, interval since HCT, and hypogonadism) or features of the intervention (final dose of NR, final training intensity in Mets per week). We will explore interactions between key variables and treatment arm. With respect to sex, we will include sex by treatment interactions in the model and explore the results of individual sex-stratified analyses, though we may lack adequate power to detect sex-specific differences {12}.

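### Interval since transplant is named as a possible driver of response but left out of the primary strength and VO2max models; pre-specifying it would be a cheap gain in precision, not the repair of an invalid analysis

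*Protocol article*

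**What the plan says.** All references are to the protocol article.

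- **Sample size and power.** Several reasons are given for expecting effects larger than published ones. One is timing after transplant: "we have chosen to intervene at the soonest potential opportunity post-HCT, thus we expect muscle deficits will be less established", with a better response to the interventions expected as a result. The others include the size of the muscle deficits and the team's experience with tailored exercise.
- **Eligibility (Table 2, inclusion criterion 4; also Table 1).** Participants enter at "6–24 months from allogeneic HCT".
- **Participants and randomization.** Stratification is by age group (under 18, or 18 and over) and site, with permuted blocks of four or eight. Interval since HCT is not a stratification factor.
- **Statistical considerations, primary model.** "We will fit a linear model with the outcome of change in Z-score of muscle strength and covariates of treatment arm and baseline Z-score". The VO2max model at the end of the section has the same form. The mixed-effects models described at the start of the section name age and sex as their time-invariant covariates.
- **Statistical considerations, secondary analyses.** Interval since HCT appears in a list of baseline covariates for additional models of change from baseline, which includes "GvHD grades II-IV, interval since HCT, and hypogonadism". The same paragraph plans exploratory interactions with treatment arm without naming the variables.

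**The concern.** The document twice treats time since transplant as relevant to the outcome: once as a reason to expect a good response, and once as a candidate explanation of change from baseline. Each participant's interval must be established at screening, because it decides eligibility. Yet neither of the two fully specified models, for strength and for VO2max, uses it.

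With about 16 completers per arm, arms can differ noticeably in mean interval by chance. If interval predicts 16-week change beyond what baseline strength already captures, the estimate in a particular trial is shifted by that imbalance, and the residual variance is larger than it need be. Power is stated as 80% for the exercise + NR versus exercise comparison, so a modest gain in precision has some value.

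**Working it through.** **Inputs from the document.** 80 randomised, 20% attrition, 64 completers, 16 per arm; 80% power for a 0.73 Z-score difference between exercise + NR and exercise; entry window 6–24 months.

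**Inputs that are assumptions.** Interval is uniform over the window. Interval explains a share R² of the residual variance left after arm and baseline Z-score. The residual SD is back-solved below, because no SD of change in strength Z-score is given (the only SD, 1.4, is for muscle area).

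**1. The plan's own figures.** 64 / (1 − 0.20) = 80, which reproduces. The power statement cannot be checked without an SD. At two-sided 0.05 it implies SD = 0.73 / [(1.960 + 0.842) × √(2/16)] = 0.737 (0.725 using t with 59 degrees of freedom). The standard error of a pairwise contrast is then 0.737 × √(2/16) = 0.26 Z.

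**2. Chance imbalance in interval.**
- SD of interval = 18/√12 = 5.20 months.
- SE of the difference between two arms of 16 = 5.20 × √(2/16) = 1.84 months; 95% range ±1.96 × 1.84 = ±3.6 months.
- P(|difference| > 3 months) = 2 × [1 − Φ(3/1.84)] = 0.10 for one contrast. With 20 per arm the SE is 1.64 months and the probability 0.07.

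**3. Shift in the estimate.** The slope per month is √R² × 0.737/5.20, so a 1-SE imbalance moves the contrast by √R² × 0.26.

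| R² (assumed) | Shift at 1 SE (1.84 months) | Shift at 3 months |
|---|---|---|
| 0.05 | 0.06 Z | 0.09 Z |
| 0.15 | 0.10 Z | 0.16 Z |

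**4. Gain from adjustment.** The confidence-interval width is multiplied by √(1 − R²), and the equivalent gain in sample size is 1/(1 − R²).

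| R² (assumed) | Width factor | Equivalent sample size |
|---|---|---|
| 0.05 | 0.975 | 1.05 |
| 0.15 | 0.922 | 1.18 |

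On the back-solved SD, power for 0.73 would rise from 80% to about 81–85% over this range, net of the lost degree of freedom.

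**5. Cost.** Four arm means and a baseline slope leave 64 − 5 = 59 residual degrees of freedom; adding interval leaves 58. An unrelated covariate inflates the variance of a contrast by roughly 1/58 on average, so break-even is near R² = 0.02. If interval is unrelated to change, the loss is under one percentage point of power.

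**6. Type I error.** In simulated two-arm comparisons with 16 per arm and R² of 0.10–0.30, the rejection rate under no effect was 0.048–0.053, whether or not interval was in the model.

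**The case against.** The strongest reply is that nothing here is wrong. Analysis of covariance on arm and baseline outcome is a standard, valid primary analysis, and chance imbalance in an unadjusted covariate is already reflected in the standard error. This stands. A reader might infer that the primary result is biased, or that an imbalance in recovery stage leaves it uncorrected in a way that threatens validity. The document does not support that, and the simulated error rates show no inflation.

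Second, a reader might infer that the 6–24 month window contradicts the claim of early intervention, or that the protocol says response depends on the month of entry. It says neither. Timing is one qualitative reason among several, and no gradient within the window is stated.

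Third, the passage on responsiveness describes effect modification, which a main-effect term does not test. This also stands, and it is why the interaction should be named. It does not remove the case for the covariate. If response varies with interval in the active arms, interval predicts change within those arms, including both arms of the exercise + NR versus exercise contrast. The protocol itself also lists interval as a candidate explanation of change from baseline.

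Fourth, baseline strength may already absorb part of any difference in recovery stage, and other listed covariates, such as GvHD grade or hypogonadism, have a claim too. Both points are fair. The first is why R² here means variance beyond baseline strength. On the second, interval is singled out because the sample-size rationale invokes timing; the document does not show that it is the strongest predictor.

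**Conclusion.** The point holds as a minor improvement in precision. A baseline variable that the protocol connects with response, and must already establish for eligibility, is reserved for exploratory models while the two main models omit it. The planned analysis remains valid.

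The size is uncertain, because the document does not quantify any association between interval and outcome. With interval uniform over the window, a 3-month imbalance has about a 10% chance in any one contrast. That is a statement about months, not about the result. At R² of 5–15%, confidence intervals would be about 2.5–8% shorter. Below about 2% there would be no gain. The shifts in Z-score and the power figures rest further on an SD back-solved from the stated power.

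**What to change.** Before unblinding, pre-specify interval since HCT at randomisation (continuous, in months) as a covariate in the strength and VO2max models under Statistical considerations. In the same section, name interval-by-arm among the exploratory interactions with treatment arm, where the variables are now unspecified, since only that term examines whether earlier participants respond more.

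The cost is one of 59 residual degrees of freedom and a very small loss of power if interval is not prognostic. Enrolment, eligibility and randomisation are unchanged. A third stratification factor is not advised: even split in two, it would turn the four existing strata into eight, averaging 80/8 = 10 participants each across four arms, which is sparse for blocks of four or eight.

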## Discussion

To our knowledge, our study represents the first intervention clinical trial to use combination of exercise and NR in AYA HCT survivors to address sarcopenia. Additionally, this trial will set the stage for the development of future studies that leverage the promise of a mitochondrial bioenergetic approach to the metabolic complications of cancer therapy. With mechanistic insights from this study, we can pursue trials to enhance clinically relevant metabolic function (e.g., glucose homeostasis that impacts risk for diabetes mellitus) in affected individuals after cancer therapy. The growing population of AYA cancer survivors (estimated to be 633,000 in the U.S. alone), makes the development of such interventions imperative, to optimize their long-term health in decades after completion of their cancer treatment [49].

We have considered a number of potential limitations and barriers that may arise in performing this study and have developed solutions in anticipation. It is possible that despite having an adequate number of potentially eligible participants (anticipated *N* = 185), we will not accrue the 80 HCT survivors over the course of the study. To address this concern, we will review and report accrual quarterly, and if recruitment is slower than anticipated, we will take several steps. Specifically, we will: 1) work with the primary treatment team to perform as many study procedures as possible during regularly scheduled clinic visit days; 2) minimize the time required for study measurements (total time commitment 6 h); and 3) provide compensation ($200) to each participant for each visit. If necessary, we can also expand the age range to 12-39y, with continued stratification of randomization by pediatric/adult status since the results may not vary significantly for those in peri-pubertal stages and those in late young adulthood.

With regards to ensuring adherence and compliance to the intervention, our team will be monitoring study participants in real-time via regular telephone check-ins and for those participating in exercise, via remote oversight, and thus be well-positioned to troubleshoot any barriers that may emerge during the conduct of the study. For NR/placebo, the investigative team will interview the adherence and intervene where necessary to ensure consistent administration of NR/placebo. Barriers to adherence can be reviewed at weekly check-ins and the interim visit. With regards to the exercise intervention, in-person orientation at the study site to exercise training using the in-home equipment will occur on the day of randomization, thus any functional or logistical limitations can be addressed in real time. To improve retention, we will offer participants randomized to the “no exercise” condition the opportunity to participate in in-home training after completion of the study {30}. Subjects who withdraw from the study will be recommended to update their medical history/concomitant medications, undergo physical exam, measure vital signs, test their clinical labs, get a DXA scan, get a 60 min MRI, perform a CPET, provide used/unused NR or placebo, and review adverse events as the early termination visit if both safe and feasible {18b}. In our team’s previous two studies of remotely supervised exercise interventions, we have demonstrated adherence rates exceeding 80% using similar procedures {11c}.

We will apply the insights gained from this trial to develop individualized, evidence-supported precision initiatives that will reduce chronic disease burden in high-risk cancer survivors. Our proposed trial is an important first step and will guide future interventions. We may also find that the benefits that accrue to skeletal muscle in response to skeletal muscle-focused interventions are recapitulated in other organ systems. For example, NAD^+^ precursors have impact on cardiac muscle, tissue that can also be adversely affected in cancer patients; in a preclinical model of dilated cardiomyopathy, NAD^+^ precursor attenuated the development of heart failure [50]. Additional metrics, such as circulatory power at peak exercise, can be measured to provide a non-invasive estimate of the circulatory system (i.e., heart rate, stroke volume, and systemic blood pressure) at peak exercise to explore such potential benefits.

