Study type	allocation: Randomized Intervention Model: Factorial Assignment Intervention Model Description: Randomized, placebo-controlled trial with a 2 × 2 factorial design testing the effects of an NAD + precursor (NR) and exercise Masking: Quadruple (Participant, Care Provider, Investigator, Outcomes Assessor) Masking Description: The participants and the investigator team will be blinded as to the group assignment: NR vs Placebo. All collected data (e.g., questionnaires) will be coded, so initial analysis will be conducted without knowledge of the participant's group status While the assignment of participants to the exercise groups will not be blinded to the participant or majority of the study team, a designated blinded technician will perform the follow-up Cardio Pulmonary Exercise Testing. Follow-Up Cardio Pulmonary Exercise Testing will be performed by a dedicated blinded study team member, an exercise technician, who will not know if the participant was assigned to an arm including the exercise intervention Phase II
Date of first enrolment	June 2022
Target sample size	80
Recruitment status	Recruiting
Primary outcome(s)	Within participant changes in muscle strength (Isometric knee extension, Z-score) [ Time Frame: Baseline to 16 Weeks]
Key secondary outcomes	Within participant change in muscle strength (Ankle Plantarflexion) using Biodex dynamometer [ Time Frame: Baseline to 16 Weeks] Within participant change in grip strength (Hand Grip Dynamometry) [ Time Frame: Baseline to 16 Weeks] Within participant changes in muscle mass (lower leg lean muscle mass by DXA) [ Time Frame: Baseline to 16 Weeks] Within participant changes in post-exercise oxidative phosphorylation capacity (OXPHOS) using non-invasive MRI scanning using creatine chemical exchange saturation transfer (CrCEST) [ Time Frame: Baseline to 16 Weeks] Within participant change in aerobic capacity (VO2 max, Maximal Oxygen Uptake on Cardiopulmonary Exercise Testing). [ Time Frame: Baseline to 16 Weeks]

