#### Dynamometry (hand grip, lower extremities)

Trained personnel will perform testing at CHOP and COH. A dynamometer (Takei Scientific Instruments Co., Ltd., Japan) will be used to measure instantaneous hand grip strength because in epidemiological studies this index of muscle strength has been shown to be associated with morbidity and mortality [28]. Three trials will be performed using each hand, and the maximum value will be recorded (N). The Biodex Dynamometer (Biodex Corp., Shirley, NY) will be used to measure muscular strength in the ankle and knee. Participant will perform isometric strength tests, with three repetitions performed at each position. A 5 s rest is given between repetitions. At each position, peak torque (N) will be recorded. References will be used to generate age- and sex-specific Z-scores [29].

*CrCEST MRI* is a non-invasive way to test skeletal muscle OXPHOS capacity [30]. With CrCEST, creatine content can be simultaneously measured in every muscle of the leg [31, 32]. CrCEST is used to determine the exponential time constant for the decline in creatine post-exercise (τCr) in each muscle of the calf (lateral gastrocnemius, medial gastrocnemius, and soleus) after an in-magnet standardized exercise on an MR-compatible. Prolonged τCr is suggestive of decreased OXPHOS capacity. In a “proof-of-principle” study using CrCEST at a 7 T MRI field strength [33], our team found that individuals with genetic diseases affecting mitochondria had significantly prolonged post-exercise τCr in the medial gastrocnemius muscle, indicating decreased OXPHOS capacity. Using CrCEST, we also found that habitual exercise duration is positively associated with muscle OXPHOS in individuals with genetic mitochondrial disorders [33]. In a separate study using CrCEST at 3 T, we found that decreased physical activity in individuals with Friedreich’s Ataxia, a neurological disorder, accounted for some of the difference in τCr in lateral gastrocnemius between individuals with Friedreich’s Ataxia and healthy controls [34]. We will use the same 3 T CrCEST to examine the effects of mitochondria-targeted interventions in the present study.

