### Harms management {22}

Safety will be monitored through the collection of laboratory assessments at baseline and follow-up. Participants will also be monitored using a standardized assessment of symptoms. We will use the Common Terminology Criteria for Adverse Events (CTCAE, version 5.0, U.S. Department of Health and Human Services) to grade AEs. Individuals who experience a new Grade 3 or higher AE that is at least possibly related to the study intervention may require cessation of study participation at the discretion of the investigative team. Grade 4 AEs will require study cessation of study participation.

If any unanticipated problems related to the research involving risks to subjects or others happen during the course of this study including serious adverse events (SAE), they will be reported to the IRB in accordance with CHOP IRB SOP 408: Unanticipated Problems Involving Risks to Subjects. AEs that are not serious but that are notable and could involve risks to subjects will be summarized in narrative or other format and submitted to the IRB at the time of continuing review. All AEs will be noted in the study records and on the case report form with a full description including the nature, date and time of onset, determination of non-serious versus serious, intensity (mild, moderate, severe), duration, causality, and outcome of the event. An AE is defined as any untoward medical occurrence in a subject who has received an intervention (drug, biologic, or other intervention), and an SAE is defined as any adverse drug experience occurring at any dose that results in death, in a life-threatening event, in a persistent or significant disability/incapacity, or a congenital anomaly/birth defect in the offspring of a subject. The occurrence does not necessarily have to have a causal relationship with the treatment. An AE can therefore be any unfavorable or unintended sign (including an abnormal laboratory finding, for example), symptom, or disease temporally associated with the use of a medicinal product, whether or not considered related to the medicinal product.

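### The early-termination visit, as listed in the Discussion, includes DXA, MRI and CPET but no dynamometry, so neither the primary knee-extension outcome nor the ankle and grip strength outcomes would be measured at exit

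*Protocol article*

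**What the plan says.** All places are in the protocol article.

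- **Exit visit (Discussion, paragraph on adherence and retention).** People who withdraw are recommended to "update their medical history/concomitant medications, undergo physical exam, measure vital signs, test their clinical labs", and then to "get a DXA scan, get a 60 min MRI, perform a CPET, provide used/unused NR or placebo, and review adverse events". The visit is conditional: "as the early termination visit if both safe and feasible".
- **Primary outcome (Statistical considerations).** "The primary outcome for our study is the change in muscle strength (quadriceps extension, Z-score) from baseline to 16 weeks". The Dynamometry section says that the Biodex device "will be used to measure muscular strength in the ankle and knee".
- **Other strength outcomes (Table 1, key secondary outcomes).** "Within participant change in muscle strength (Ankle Plantarflexion) using Biodex dynamometer", and a hand-grip dynamometry measure.
- **Analysis (Statistical considerations).** Two models are described. One is a linear mixed-effects model, said to allow all randomized participants to be included. The other is a linear model for change in strength Z-score, with treatment arm and baseline Z-score as covariates. The two-stage testing procedure is described with the second model.
- **Stopping (Harms management).** "Grade 4 AEs will require study cessation of study participation". A new Grade 3 or higher event that is at least possibly related may also lead to cessation, at the team's discretion.
- **Attrition (Sample size and power).** 80 are randomized so that 64, or 16 per arm, have complete data.

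**The concern.** The exit list is specific. It includes a scan of 60 minutes and a maximal exercise test, yet leaves out the test on which the trial's main conclusion rests. Followed literally, a person could attend the exit visit, complete a CPET and still leave no exit strength value.

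The change-score model needs a post-baseline strength value, and a person without one cannot enter it. Harms management ends study participation, not only the intervention, after some adverse events. No section says that these people are still asked for week-16 outcomes, so the exit visit is the only route to a late measurement that the article describes for them.

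Exercise assignment is not blinded to participants (Participants and randomization). It is therefore plausible, though not documented, that leaving depends on arm or on response. If so, the loss would bias the comparison as well as cost precision.

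**Working it through.** **1. Outcomes set against the exit list**

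| Outcome (Table 1) | Test | On exit list? |
|---|---|---|
| Knee extension (primary) | Biodex dynamometry | No |
| Ankle plantarflexion | Biodex dynamometry | No |
| Hand grip | Grip dynamometry | No |
| Lower-leg lean mass | DXA | Yes |
| OXPHOS | CrCEST MRI | Yes |
| VO2max | CPET | Yes |

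All three strength outcomes are absent and all three others are present. What is missing is a whole test modality.

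**2. The plan's attrition figure**

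- 64 / (1 - 0.20) = 80, which reproduces the stated number randomized.
- Expected leavers: 80 x 0.20 = 16, or 16 / 4 = 4 of 20 per arm if spread evenly.

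**3. What each model can use**

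- Change-score model: a person with only a baseline value has no outcome and is excluded.
- Mixed model: the person can be included formally, but a baseline value alone carries essentially no information on that person's change.

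**4. Illustrative bias**

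The assumption, which has no source in the documents, is that leavers' mean change lies d = 0.5 to 1.0 Z below that of completers in the same arm. With a fraction p leaving:

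- mean over everyone = completer mean - p x d
- excess of the completer mean = p x d = 0.20 x 0.5 = 0.10 Z, up to 0.20 x 1.0 = 0.20 Z
- relative to the 0.73 Z difference in Sample size and power: 0.10 / 0.73 = 14%, up to 0.20 / 0.73 = 27%

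The bias in a contrast is p1 x d1 - p2 x d2. It reaches 0.10-0.20 Z only if the comparison arm has no such bias, and it is zero if both arms lose similar people in similar numbers.

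**5. Upper bound on recoverable precision**

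The article gives 80% power for 0.73 Z (exercise + NR against exercise) but no SD of change, so the power cannot be checked directly. The implied SD at 16 per arm is

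SD = 0.73 / [sqrt(2/16) x (z for two-sided alpha + z for 80% power)]

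| Two-sided alpha | Implied SD | Power at 16 per arm | Power at 20 per arm |
|---|---|---|---|
| 0.05 | 0.74 | 80% | 87.9% |
| 0.025 | 0.67 | 80% | 88.6% |
| 0.0167 | 0.64 | 80% | 88.9% |

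If all 16 leavers gave fully usable values, power would rise from 80% to about 88-89%. The real gain would be smaller, because not all would attend and an exit value is not a week-16 value.

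**The case against.** The strongest reply is that the point rests on one sentence in the Discussion of a journal article. The schedule of procedures is Table 3, whose content is not in the text available here, and it may list dynamometry at early termination. This stands as a condition: if Table 3 has the test, what remains is a text correction. It does not remove the point, because the Discussion gives an itemised list that a site could follow as written.

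A second reply is that an exit test in, say, week 3 does not supply the primary outcome, which is defined at week 16, and that the change-score model has no stated way to use it. This also stands, and the fix therefore has to say how such a value is analysed.

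Third, attrition is partly handled: the sample size allows for it, and the plan will compare completers with non-completers. That protects power and describes who left. It does not remove bias from informative loss.

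A reader might infer more than the documents support:

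- *That the primary outcome alone was dropped.* Ankle and grip strength are missing too.
- *That leavers never have a strength value.* Baseline is measured. There is an on-site week-8 visit, and Study assessments places the tests at baseline and follow-up visits without saying whether week 8 counts. The Abstract points to baseline and week 16 only. A week-8 strength value is thus neither stated nor excluded.
- *That those stopped for adverse events are barred from the exit visit.* Nothing says so.

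**Conclusion.** The point holds in limited form. As listed, the exit visit collects DXA, MRI and CPET but no strength measure, so the primary outcome and two key secondary outcomes would not be captured at exit. Up to about 16 of 80 participants could lack a post-baseline strength value and drop out of the change-score model. That number assumes that attrition is 20% as planned, that Table 3 does not already list the test, and that no week-8 strength value exists.

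It would be wrong to conclude that the sample size or power is in error, since 80 was chosen to leave 64 with complete data. It would also be wrong to read 14-27% of the target difference as an estimate of bias. That range follows from an assumed deficit in one arm with none in the comparator, and it credits the omission with all the loss, although some leavers would not attend any visit. The direction and size of the actual bias are unknown. The established harm is an avoidable loss of primary-outcome data, with possible bias if leaving is related to arm or response.

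**What to change.** 1. Add knee-extension dynamometry, with ankle and grip, to the early-termination list in the Discussion. If Table 3 already has it, correct the text to agree.
2. State that people who stop an intervention are asked to attend the week-16 strength assessment if it is safe and they are willing, and are analysed in their assigned arm. Reconcile this with Harms management, which speaks of ending study participation, by saying which outcome measurements, if any, are still sought. The clinical stopping criteria stay as they are.
3. State how an exit value before week 16 is used, for example in the mixed model at its actual time or in a sensitivity analysis, and whether strength is measured at week 8.

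**Cost.** The exit visit becomes slightly longer. The article gives no duration for the test but describes three repetitions per position with 5 s rests, performed at both sites. Item 1 is a short text change. Items 2 and 3 need a little more drafting, because item 2 touches the definition of participation. Exit values will be only partly informative about week 16. The Trial status section says recruitment had not commenced, although Table 1 gives the status as recruiting; the change is cheapest before the first withdrawal.
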